#### Relationship between effect of tDCS and patient’s level of function

All the data collected during the clinical and functional tests and the gait analysis will be used to establish the functional level of each patient and to check whether the effects of tDCS are the same for all patients with different functional levels recovery or if they depend on initial functional level.

### Statistical analysis

The details of calculation of the COM and the COP are available in the ‘Appendix’ section.

The sample size was calculated from the data by Bonnyaud et al. (2016) [24]. Bonnyaud et al. [24] studied the raw trajectory length of patients with hemiparesis compared to a group of healthy subjects during a gait task (Timed Up and Go Test), which is very similar to what we will do by evaluating the variability of the COM during gait. Based on the data of Bonnyaud et al. [24], there was a difference of 99.5 cm in the trajectory lengths of the patients with stroke and the healthy subjects. In the present study, we hope to find a reduction in this difference following anodal tDCS; however, following placebo tDCS, there should be no difference. To determine the size of the sample of patients, we used the standard deviations of the patients with hemiparesis included in the study by Bonnyaud et al. [24].

In order to obtain a 50 to 60% reduction of the difference in COM variability between anodal and placebo tDCS with a power of 90% and a moderate to large effect size, a sample of 39 subjects is necessary. We therefore decided to include 40 patients in order to cover any drop outs. All the calculations were carried out using XLSTAT 2016® with a threshold of 90% power and a significance of *α* = 0.05.

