#### Analysis of outcome measures

Patient characteristics (age, gender, etc.) will be described by means, medians and standard deviations for continuous numeric parameters and by frequency tables with 95% confidence intervals for qualitative parameters.

A chi-squared test with Yates’ correction or the Fisher’s exact chi-squared test will be used to compare the distributions of qualitative variables.

There will be two possibilities for quantitative and ordinal variables:If the data are close to a normal distribution, means will be compared using Student’s *t* test

Comparison of the means or medians will be carried out for all the functional clinical data and the data determined following the movement analyses during the different evaluations. Repeated measures analysis of variance (ANOVA) and/or analysis of covariance as well as *t* tests (and/or non-parametric sign tests), corrected using the Scheffé adjustment, will be used for multiple comparisons.2.If the variables do not follow a normal distribution or if the small number of subjects studied does not allow the normality to be determined, we will use non-parametric tests such as Wilcoxon for the comparison of two variables, or Kruskall-Wallis for the comparison of more than two variables

All tests will be carried out with a bilateral threshold of first order of 5%.

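### The 90% power quoted for 39 patients is not supported for the trial's own primary, within-patient comparison and cannot hold across the stated range of effects

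*Protocol article*

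**What the plan says.** All references are to the Protocol article.

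- **Statistical analysis, source of the effect.** The cited study "studied the raw trajectory length of patients with hemiparesis compared to a group of healthy subjects during a gait task", the Timed Up and Go Test. The gap between patients and healthy subjects was 99.5 cm. The article regards this task as close to its own measurement of COM variability during gait.
- **Statistical analysis, source of the SD.** "we used the standard deviations of the patients with hemiparesis included in the study". No value is printed.
- **Statistical analysis, result.** For a reduction of 50 to 60% in the anodal-versus-placebo difference in COM variability, "with a power of 90% and a moderate to large effect size, a sample of 39 subjects is necessary". The software was run "with a threshold of 90% power and a significance of" 0.05. On attrition: "We therefore decided to include 40 patients in order to cover any drop outs".
- **Primary outcomes.** The outcome is variability of COM displacement in gait and trajectory tracking, and variability of COP displacement in static balance. It is recorded four times at each stimulation visit.
- **Study design.** Randomised cross-over; every patient has one anodal and one placebo visit, 7 days apart.
- **Analysis of outcome measures.** Repeated-measures ANOVA and/or ANCOVA, with t tests or sign tests "corrected using the Scheffé adjustment, will be used for multiple comparisons". "All tests will be carried out with a bilateral threshold of first order of 5"%.

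**The concern.** The sample-size paragraph and the trial it sizes differ in four respects.

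1. **Outcome.** Path length in centimetres is not variability of displacement, and nothing in the calculation concerns COP in static balance.
2. **Contrast and SD.** The 99.5 cm separates patients from healthy people, and the SD is the spread between patients. A cross-over is powered by the SD of each patient's anodal-minus-placebo difference. No within-patient SD or correlation is given.
3. **Effect.** One n at one power is given for a range of effects.
4. **Error rate.** The calculation is at an unadjusted 0.05, while the analysis plans Scheffé-corrected comparisons and does not say whether the primary contrast is one of them.

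At stake is how a null result is read. The Discussion (Impact) says that if no effect is seen and no robust explanation emerges, this would suggest that anodal tDCS does not affect gait or balance. That inference needs a power figure that belongs to the comparison actually made.

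**Working it through.** **Reproducing 39.** A forward calculation is not possible: the article prints no SD, no single effect, no correlation and no named test. I solved backwards instead. For a paired t test, two-sided 5%, power is P(|T| > t₀.₉₇₅,ₙ₋₁), with T noncentral t on n − 1 df and noncentrality d√n, where d is the mean difference divided by the SD of within-patient differences.

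- n = 39 gives 90% at d = 0.533 (noncentrality 0.533 × √39 = 3.33).
- A two-sample t test with 39 per group gives 90% at d = 0.744.

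Both values can be called moderate to large, so the text does not show which test was used. The rest takes the paired reading, because it matches the design.

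**The 50 to 60% range.** With the SD fixed, d is proportional to the reduction.

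| If 39 was set for | d at the other end | Power at the other end, n = 39 | n for 90% there |
|---|---|---|---|
| 60% | 0.533 × 50/60 = 0.444 at 50% | 77% | 56 |
| 50% | 0.533 × 60/50 = 0.639 at 60% | 97% | 28 |

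This step needs no assumption about the SD or correlation beyond d = 0.533 at the chosen end.

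**Between-patient SD in a cross-over.** Let σ be the between-patient SD and ρ the within-patient correlation. The SD of paired differences is σ√(2(1 − ρ)), which equals σ only at ρ = 0.5. If σ was entered as the paired SD, the true d is 0.533/√(2(1 − ρ)). The values of ρ are assumptions; the article gives none.

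| ρ | d | Power, n = 39 |
|---|---|---|
| 0.3 | 0.450 | 78% |
| 0.5 | 0.533 | 90% |
| 0.7 | 0.688 | 99% |

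**Scheffé.** The critical value for k means is √((k − 1)F₀.₉₅;ₖ₋₁,df), with power from the noncentral t on the same df and noncentrality 3.33. The error df is not stated, so both n − 1 = 38 and (k − 1)(n − 1) are shown. The standardised effect stays at 0.533.

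| Means compared | Critical value, df 38 / df (k − 1)38 | Power, n = 39 |
|---|---|---|
| 2 (the two conditions) | 2.02 / 2.02 | 90% |
| 4 (for example, four times) | 2.92 / 2.84 | 66% / 69% |
| 8 (two conditions × four times) | 3.98 / 3.78 | 28% / 33% |

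**Attrition.** At d = 0.533, power is 90.7% with 40 completers, 89.2% with 38 and 87.4% with 36.

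**The case against.** **Nothing here shows that 39 is wrong.** A reader might infer that the trial is underpowered, or that the design does not deliver 90%. The documents do not support either. Without the SD, correlation and test, 39 can be neither reproduced nor refuted. A between-patient SD is conservative once ρ exceeds 0.5, so power could exceed 90%. This objection stands, and the point is limited to it: the figure is unsupported, not disproved.

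**A moderate-to-large effect is compatible with 39.** True: 0.533 lies between the conventional 0.5 and 0.8, so that phrase contradicts nothing. The 50 to 60% range is another matter, because it is a range on the trial's own scale with a single n and a single power.

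**The proxy is declared, and path length is measured.** The Secondary outcomes section does include COM trajectory length in the path-following task, and the article states openly that it regards the tasks as similar. But that same section lists length and oscillations separately, the Timed Up and Go is only a secondary functional test, and path length says nothing about COP variability in static balance.

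**The Scheffé loss is conditional.** Agreed. The article applies the correction to multiple comparisons generally. A two-mean contrast, or an ANOVA F test at 5%, loses nothing. It would be wrong to read 28–33% as what the plan commits to.

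**Attrition is minor.** Agreed: three patients fewer than 39 costs under 3 percentage points.

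**Conclusion.** The claim of 90% power with 39 patients is not supported for the primary comparison. The effect and SD belong to another measure and another kind of contrast, and one n cannot give 90% power at both 50% and 60%: the other end of the range has 77% or 97%. The second of these faults rests only on the paired t test and d = 0.533 at one end.

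The true power is unknown in both directions. It is 78% to 99% for assumed ρ of 0.3 to 0.7 if the between-patient SD was used as the paired SD. It is 90%, 66–69% or 28–33% if the primary contrast is Scheffé-corrected over 2, 4 or 8 means at the same standardised effect. These are conditional scenarios, not estimates for this trial.

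Should-fix: the number of patients need not change, but the stated power cannot bear the no-effect conclusion that the Discussion would rest on it.

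**What to change.** Keep 40 patients and make these changes before unblinding.

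1. Restate the power along these lines: *39 completers give 90% power, two-sided 5%, paired, for an anodal-minus-placebo difference of 0.53 SD of the within-patient differences, on [one named primary measure] at [one named time point], tested without Scheffé correction; 36 completers give 87%.*
2. Remove the 50 to 60% range, or tie the power to a single value. Stop presenting path length as the basis for the variability outcome.
3. Estimate the within-patient SD, blind to condition, from the inclusion-visit measurement and the pre-stimulation measurements at the second and third visits. Report the detectable difference in the outcome's own units. The 0.53 is solved back from 39 and carries no clinical rationale of its own; this step gives it a meaning that clinicians can judge.
4. Keep the multiplicity correction for the remaining time points and outcomes.

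The cost is rewording and a small blinded calculation on data already planned, with no extra patients or visits. The downside is that the stated power may become less favourable.

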#### Analysis of outcome measures

Patient characteristics (age, gender, etc.) will be described by means, medians and standard deviations for continuous numeric parameters and by frequency tables with 95% confidence intervals for qualitative parameters.

A chi-squared test with Yates’ correction or the Fisher’s exact chi-squared test will be used to compare the distributions of qualitative variables.

There will be two possibilities for quantitative and ordinal variables:If the data are close to a normal distribution, means will be compared using Student’s *t* test

Comparison of the means or medians will be carried out for all the functional clinical data and the data determined following the movement analyses during the different evaluations. Repeated measures analysis of variance (ANOVA) and/or analysis of covariance as well as *t* tests (and/or non-parametric sign tests), corrected using the Scheffé adjustment, will be used for multiple comparisons.2.If the variables do not follow a normal distribution or if the small number of subjects studied does not allow the normality to be determined, we will use non-parametric tests such as Wilcoxon for the comparison of two variables, or Kruskall-Wallis for the comparison of more than two variables

All tests will be carried out with a bilateral threshold of first order of 5%.

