### Inclusion criteria

Patients will be included if they fulfil the following inclusion criteria: adult man or woman aged 18 years or older, with hemiparesis following unilateral hemispheric cerebral lesions of vascular origin more than 6 months previously, able to walk for 10 min non-stop with no gait aids, having provided informed consent.

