### Primary outcomes

#### Before, during, immediately after, and 30 min after tDCS cessation

Variability of the COM

As previously indicated, the variability of COM displacement is a strong marker of dynamic stability during locomotion and it is altered in patients with stroke.

The primary outcome measure of this study is thus the assessment of the variability of the displacement of the COM during gait and during trajectory tracking over the ground, evaluated by 3D gait analysis and the variability of the displacement of the COP during a static-balance task on a force platform. It will be recorded once during the inclusion visit then four times during the stimulation visits: before, during, immediately after and 30 min after cessation of stimulation. A reduction in the variability of COM displacement should result in an improvement of spatiotemporal, kinematic and kinetic gait parameters.

The 3D gait analysis will be conducted with a 3D optoelectronic system (Motion Analysis Corporation, Santa Rosa, CA, USA, sampling frequency 100 Hz) with eight optoelectronic cameras. Thirty markers will be placed on the patient’s body (following the Helen Hayes model commonly used by the biomechanical community for gait analysis [53]). The relative displacement of each segment will be calculated from these coordinates (flexion/extension, abduction/adduction, internal/external rotation). The marker trajectories will then be filtered using a fourth-order zero-lag Butterworth low-pass-filter, with a 6-Hz cut-off frequency [54]. The data from two force platforms combined with the kinematic and anthropometric data will be used to evaluate the displacement of the COP and COM during gait and balance tasks.Instrumented gait task

Ten trials of gait at a comfortable speed and 10 trials at maximal speed will be recordedInstrumented balance task

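### If the listed repeated-measures ANOVA is run in its classical form over all eight assessments, one missing assessment removes the whole patient, and the sample size has room to lose only one

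*Protocol article*

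**What the plan says.** Under Primary outcomes, the protocol article has the variability of centre-of-mass and centre-of-pressure displacement recorded once at inclusion and then "four times during the stimulation visits: before, during, immediately after and 30 min after cessation of stimulation". Study design sets two such visits, anodal and placebo in random order, 7 days apart.

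Under Analysis of outcome measures, the functional clinical data and the movement-analysis data share one list of methods: "Repeated measures analysis of variance (ANOVA) and/or analysis of covariance as well as" t tests and/or sign tests, with a Scheffé correction for multiple comparisons. Wilcoxon or Kruskal-Wallis tests replace these if normality fails or cannot be judged. The article does not give the factors or levels of the ANOVA, does not name one model for the primary outcome, and states no rule for a patient with a missing assessment.

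Under Statistical analysis, "with a power of 90% and a moderate to large effect size, a sample of 39 subjects is necessary", and 40 are to be included to cover drop-outs.

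**The concern.** Classical repeated-measures ANOVA needs a full row per patient. Run over both visits and all four time points, it discards anyone with one empty cell, including their valid measurements. A patient who completes everything except the last battery of one visit would contribute nothing.

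Unfinished visits are plausible from the protocol's own workload. Patients qualify if "able to walk for 10 min non-stop with no gait aids". At each time point the instrumented battery includes 20 gait trials, 20 step initiations, standing with eyes open and closed, a figure-of-8 path and six obstacle crossings. Functional tests, including stairs and a 6-minute walk, are done before and after stimulation.

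Power is at stake, because the analysed number could fall faster than actual withdrawal. Bias is also possible. If less able walkers are the ones with gaps, and the effect depends on functional level (which the article itself plans to examine), the complete patients would not represent those randomised.

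**Working it through.** **Inputs from the article.** Two stimulation visits with four assessments each; two-sided 5% level; 90% power; 39 needed and 40 included; target effect 50 to 60% of a 99.5 cm difference. The standard deviation comes from a cited study and is not printed ("we used the standard deviations of the patients with hemiparesis included in the study by" that study). No missingness rate is given, so every rate below is an assumption.

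**1. Number of cells.** 2 visits × 4 time points = 8 assessments under stimulation or placebo, plus one at inclusion.

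**2. The plan's own figure.** Without the standard deviation, 39 cannot be reproduced directly, so the standardised effect is back-solved. For a paired t test, power = P(T > t₀.₉₇₅,ₙ₋₁), where T is noncentral t with n − 1 degrees of freedom and noncentrality d√n. Setting power to 0.90 at n = 39 gives d = 0.533. The normal approximation is (1.960 + 1.282)/√39 = 0.519.

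The target effect is 0.50 × 99.5 = 49.75 cm to 0.60 × 99.5 = 59.7 cm. The implied standard deviation of the paired difference is therefore 49.75/0.533 ≈ 93 cm to 59.7/0.533 ≈ 112 cm. The same formula needs 44 patients at d = 0.5 and 37 at d = 0.55, so 39 fits the article's description of a moderate to large effect.

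**3. Reserve.** 40 − 39 = 1 patient, or 1/40 = 2.5%.

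**4. Complete patients under an eight-cell complete-case ANOVA.** Let v be the share of visits whose last battery is unfinished, independent between the two visits. Expected complete patients = 40(1 − v)². Power is the paired t power at d = 0.533, with the count rounded down; it stands in for the ANOVA contrast, whose variance structure is not given. The number to enrol for 39 complete is 39/(1 − v)², rounded up.

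| v (assumed) | (1 − v)² | Complete of 40 | Power | Enrol for 39 complete |
|---|---|---|---|---|
| 2.5% | 0.951 | 38.0 | 89% | 42 |
| 5% | 0.9025 | 36.1 | 87% | 44 |
| 10% | 0.81 | 32.4 | 83% | 49 |
| 15% | 0.7225 | 28.9 | 78% | 54 |

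At v = 5%, the chance of at least 39 complete patients is 0.9025⁴⁰ + 40 × 0.0975 × 0.9025³⁹ ≈ 0.017 + 0.071 ≈ 0.09.

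**5. If the same patients fail at both visits.** With full clustering, complete patients = 40(1 − v): 38 at 5% (power 89%) and 36 at 10% (power 87%). The range between full clustering and independence is therefore 36 to 38 patients at 5%, and 32 to 36 at 10%.

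**6. Paired tests instead.** If only the 30-minute battery is missing, anodal-versus-placebo comparisons before, during and immediately after stimulation keep all 40 patients. Only the 30-minute comparison loses those in the table. A patient with just one stimulation visit is lost from every paired comparison between conditions.

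**The case against.** The strongest reply is that the article does not fix the analysis being criticised. Its methods form an and/or list; the ANOVA could be run on changes, within a condition or on fewer time points; and deletion of incomplete patients is nowhere written. This stands, and it is why the point is conditional. A reader might infer that the plan removes tired patients from its primary analysis, but the text does not support that.

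The link to fatigue is also an inference. The article lists fatigue only as a possible sensation during stimulation. It gives no rate or pattern of early stopping, and a condensed article may omit rest breaks. Patients must already walk 10 minutes unaided, and they do one instrumented battery before randomisation, which offers partial reassurance. A shift towards fitter walkers is therefore possible but not shown, and no bias can be quantified.

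A reader might also reach larger losses by letting each of the eight cells fail independently: 40 × 0.98⁸ ≈ 34 complete patients (power 85%) at 2% per cell, and 40 × 0.95⁸ ≈ 26.5 (power 74% at 26, 76% at 27) at 5%. Those figures are at the upper end. If fatigue is the cause, gaps cluster in the same patients and the last battery, which leaves more complete patients at the same per-cell rate.

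Finally, handling of missing data is commonly left to a full protocol or analysis plan, so the absence of a rule here is not a fault. What remains is narrower: a method the article does name fits an eight-assessment cross-over with one spare patient poorly, and the alternatives it lists only partly make up for that.

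**Conclusion.** The point holds conditionally. If the repeated-measures ANOVA is run classically over all eight assessments, any patient with one gap is lost, and the reserve of one patient cannot absorb even modest incompleteness. With the last battery unfinished in an assumed 5% or 10% of visits, independently at the two visits, about 36 or 32 patients remain, with power of about 87% or 83% instead of 90%. Clustering of gaps would soften this, and paired tests at single time points would lose fewer patients.

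These figures rest on assumed rates and on a paired effect of 0.533 back-solved from the stated 39. This is a moderate loss of power that is easily avoided. It does not show that the planned analysis is invalid.

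**What to change.** Name one primary analysis: a likelihood-based linear mixed model on all recorded assessments, with fixed effects for condition, time, condition by time, period and sequence, and random effects for patient and for visit within patient. Period and sequence belong in the model because this is a two-period cross-over. Keep the complete-case repeated-measures ANOVA as a sensitivity analysis. Recording the reason for each unfinished battery, by condition, would help in judging the missing-data assumption.

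The cost is a change of wording and a little more analysis work, with no new data beyond those reasons. The model assumes that missingness depends only on observed data (missing at random). That is weaker than the missing-completely-at-random condition that the complete-case ANOVA generally needs. The gain in precision cannot be computed, because no variances or correlations are given. It will be small for patients with only one stimulation visit, who add little to a within-patient contrast.

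### The test is chosen after the data are seen, by whether the measured variables look normal; in this cross-over the check belongs on within-patient differences or residuals, and one named fallback ignores pairing

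*Protocol article*

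**What the plan says.** Under Analysis of outcome measures, the protocol article gives two routes for quantitative and ordinal variables. If the data are close to normal, means are compared by Student's t test, with repeated-measures ANOVA and/or ANCOVA, and t tests or sign tests with a Scheffé adjustment for multiple comparisons. "If the variables do not follow a normal distribution", or if there are too few subjects to judge, the tests become Wilcoxon for two variables or Kruskal-Wallis for more than two. No normality test or cut-off is named. The Wilcoxon test is not said to be the signed-rank form. Tests are two-sided at 5%.

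The Study design section describes a cross-over with two stimulation visits 7 days apart. Under Primary outcomes: "The primary outcome measure of this study is thus the assessment of the variability of the displacement of the COM during gait", together with trajectory tracking and centre-of-pressure variability in static balance. Each is recorded before, during, immediately after and 30 min after stimulation. The sample-size text reads "In order to obtain a 50 to 60% reduction of the difference in COM variability between anodal and placebo tDCS" and continues "with a power of 90% and a moderate to large effect size, a sample of 39 subjects is necessary".

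**The concern.** Three things go wrong in one rule.

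- **Wrong object.** The rule speaks of the variables, and the sentence introducing it uses that word for the measured quantities. Their spread across patients includes the stable differences between patients, which cancel in a within-patient comparison. A skewed mix of mild and severe patients can fail the check although the paired differences satisfy the t test's assumption.
- **Late choice.** The method is settled from outcome data, variable by variable, with no criterion. Primary measures may end up tested by different methods.
- **Unsuitable fallback.** Kruskal-Wallis assumes independent groups. Used on repeated measurements of the same patients, it leaves between-patient spread in the noise. It also has no condition-by-time term, although the Discussion (Impact) expects the comparison over time to show the kinetics of the stimulation effect.

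At stake is the precision for which a cross-over is chosen.

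**Working it through.** **Inputs from the protocol article.** Two-sided alpha 0.05, power 90%, 39 needed and 40 included. The reference is "there was a difference of 99.5 cm in the trajectory lengths of the patients with stroke and the healthy subjects". The standard deviation (SD) is described ("we used the standard deviations of the patients with hemiparesis included in the study") but no number is given. No distribution, coefficient of variation (CV) or within-patient correlation is given for any primary measure, so all of these are assumed below.

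**The plan's own figure.** Paired t power comes from the noncentral t distribution with n − 1 degrees of freedom and noncentrality d√n. For n = 39 and power 0.90 this gives d = 0.533; d = 0.50 needs 44 and d = 0.60 needs 32. If the target is 50 to 60% of 99.5 cm (49.75 to 59.7 cm), the implied SD of differences is 49.75/0.533 ≈ 93 to 59.7/0.533 ≈ 112 cm. So 39 is compatible with a paired t test and a moderate effect, but cannot be verified. At n = 40 and d = 0.533, power is 0.907.

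**Check A: the rule can fail while the assumption holds.** Simulation, n = 40, up to 3,000 runs per setting. Patient levels are lognormal (median 1). Within-patient error is normal with SD 0.05, 0.10 or 0.15, and the effect is additive with d = 0.533 on the differences. Runs with non-positive values were dropped (1,556 to 3,000 kept). The paired differences are normal by construction. Ranges run over the three error SDs.

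| Between-patient log-SD | Shapiro-Wilk rejects either condition | Rejects paired differences | Paired t | Signed-rank | Paired t on logs | Kruskal-Wallis |
|---|---|---|---|---|---|---|
| 0.2 | 20–30% | 5–6% | 0.90–0.91 | 0.89–0.90 | 0.886–0.894 | 0.00–0.48 |
| 0.3 | 42–52% | 5–6% | 0.90–0.91 | 0.89–0.90 | 0.854–0.889 | 0.00–0.17 |
| 0.5 | 84–87% | 4–6% | 0.90–0.91 | 0.89 | 0.785–0.809 | 0.00–0.01 |
| 0.7 | 97–98% | 5–6% | 0.90–0.91 | 0.90 | 0.710–0.733 | 0.00 |

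**Check B: lognormal data with a multiplicative effect.** n = 40, 1,500 runs per setting, within-patient correlation 0.5 or 0.8, log-scale d = 0.533. The plan's rule is taken as signed-rank if either condition fails Shapiro-Wilk, otherwise paired t.

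| CV | Rejects one variable | Rejects either condition | Rejects paired differences | Plan's rule | Paired t on logs | Kruskal-Wallis, corr. 0.5 / 0.8 |
|---|---|---|---|---|---|---|
| 0.15 | 16% | 25–28% | 7% | 0.89–0.90 | 0.90–0.91 | 0.66 / 0.16 |
| 0.3 | 47–48% | 63–70% | 17% | 0.89 | 0.91–0.92 | 0.67 / 0.16 |
| 0.5 | 82% | 94–96% | 41–45% | 0.87–0.88 | 0.91–0.92 | 0.69 / 0.16 |
| 0.7 | 96% | over 99% | 66–71% | 0.85–0.86 | 0.89–0.90 | 0.68 / 0.17 |
| 1.0 | over 99% | 100% | 85–90% | 0.84–0.85 | 0.91 | 0.67 / 0.16 |

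The rule with signed-rank therefore loses about 1 to 3 points up to CV 0.3 and about 4 to 7 points at CV 0.5 to 1.0.

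**Check C: why ignoring pairing is costly.** An unpaired test uses a standard error too large by 1/√(1 − ρ), where ρ is the within-patient correlation. Approximate power is Φ(d√n − 1.96/√(1 − ρ)), with d√n = 0.533 × √40 = 3.37.

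- ρ = 0.5: 3.37 − 2.77 = 0.60, power 0.73.
- ρ = 0.8: 3.37 − 4.38 = −1.01, power 0.16.

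This agrees with the simulations, where ranking costs a little more at ρ = 0.5. The Kruskal-Wallis figures are for two conditions, where the test is the unpaired Wilcoxon rank-sum test (in Check A the two agreed within 0.01). They therefore also show the cost if the unspecified Wilcoxon were the unpaired form. For more than two sets of measurements they illustrate the mechanism and are not exact.

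**The case against.** The strongest reply is that an article condenses the plan. Transformations, residual checks and the exact form of Wilcoxon are commonly left to an analysis plan that is not shown, and the word variables could be meant to cover paired differences. If the fallback is signed-rank, the rule does little harm: the loss is a few points, and in a simulation of that reading over 20 settings its type I error stayed between 0.041 and 0.057. A signed-rank test on each patient's difference in change from baseline would also address condition by time. All this is fair, and it is why the omission of a transformation is not itself the point. It does not rescue a stated rule that points at the measured variables and names Kruskal-Wallis for repeated measurements.

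A reader might go further in three ways that the article does not support.

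- **That the primary measures will nearly always fail the check.** No distribution is given. At CV 0.3 a single variable fails in just under half of trials, at CV 0.15 in 16%.
- **That a log-scale analysis should be mandatory.** It wins in Check B because the data were generated to suit it. In Check A it falls to 0.71–0.89 while the raw paired t test stays near 0.90. The sample-size target is a percentage reduction of a difference, anchored to a gap in cm, so it does not imply an anodal/placebo ratio.
- **That the 90% power belongs to an analysis the rule will usually discard.** The sample-size text names no test; the paired t test is inferred by back-solving.

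**Conclusion.** The point holds as a defect in how the rule is fixed. The check is on the wrong object, the method is chosen after the data are seen, and one named fallback does not fit a cross-over. How often the rule would change the test cannot be known from the article.

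The size depends on which fallback is used: about 1 to 7 points of power for signed-rank under assumed lognormal data (CV 0.15 to 1.0), against power of about 0 to 0.69 instead of about 0.90 for a test that ignores pairing. The latter range rests on assumed correlations from 0.5 upwards. The error is one of lost power, not of false positives: with positive correlation the unpaired test is conservative. It is worth correcting because the remedy is cheap, but it does not show that the trial is underpowered.

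**What to change.** Delete the rule that lets the normality of the variables choose the test. In its place, state in advance:

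1. One within-patient cross-over model for all primary measures, with condition, period, time, condition-by-time and patient.
2. Assumptions checked on model residuals or paired differences.
3. The Wilcoxon signed-rank test, named as such, on within-patient anodal-placebo differences as a sensitivity analysis only.
4. No Kruskal-Wallis test on repeated measurements of the same patients.
5. The scale, raw or log, fixed beforehand from blinded or earlier data. The inclusion visit and the pre-stimulation recording at the first stimulation visit would serve, since both precede any stimulation. Logs should not be mandated: they gain a few points if effects are multiplicative and lose more if effects are additive.

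The cost is a few sentences in the statistical section and the analysis plan and slightly more modelling work. No extra data are needed.
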